**Figure 2 figure2:**
[figure not shown]
The proposed study according to the five-step process described by the Medical Research Council framework for developing complex interventions [42].

#### Experimental Group: Smartphone Peer Physical Activity Counseling

The SPPAC program comprises 14 weekly sessions (~30 min) delivered by a peer trainer over 10 weeks. Feedback from focus groups indicated a desire for increased frequency of contact at the beginning and end of program; therefore, two sessions per week will be held during weeks 1 through 3 and week 10 [34]. Peer trainers, who are physically active manual wheelchair users with at least 5 years’ experience using a manual wheelchair, will consult a study investigator throughout program implementation as needed. A minimum of two peer trainers will receive comprehensive training in a 2-day workshop from study investigators ([name]) that will include education about adapted PA, PA using a manual wheelchair, manual wheelchair skills training, behavioral counseling techniques, goal setting and motivational strategies, and possible risks associated with PA among manual wheelchair users (eg, spasms, blood pressure changes, unsafe transfers).

The peer trainer will deliver the SPPAC program through voice or video calls (depending on participant preference) using a mobile phone. Video calls will be the preferred approach because face-to-face interactions may reinforce vicarious experiences (eg, the peer trainer may demonstrate how to accomplish a specific task using their wheelchair). However, preference for voice calls will be accommodated. Participants will be encouraged to visit a SPPAC private Facebook page that can be accessed through the mobile phone. The Facebook page will encourage interaction with peer trainers and other participants, creating a social network for sharing stories and pictures of PA participation, monitoring goal progression, and discussing successes and barriers. Cultivating online social networks has been shown to have a large effect on motivation for PA [33].

The initial SPPAC session will focus on rapport development and getting to know the participant. An exchange of dialog will include introductions, discussion of interests, likes and dislikes, benefits of PA, current activities performed, and PA goals and motives. The peer trainer will assist with defining PA goals for the following week and developing an action plan (eg, overcoming barriers, sources of social support [ie, SPPAC Facebook page], rewards). The peer trainer will keep a log of PA goals and action plans for each participant, and participants will also be encouraged to monitor their own goal progression (eg, writing goals and action plans). Goal setting will follow the SMART goal framework [42].

The remainder of the sessions will follow a standardized format of (1) 30-minute calls to review the previous week (ie, what worked/did not work, identify challenges and how they were overcome/not overcome, review/add PA goals), (2) integration of motivational strategies (eg, provide choices to modify the program to suit their individual preferences [13], brainstorm ways of making activities more enjoyable), and (3) develop action and coping plans [11,12] for the next week. The final session will follow the same format, but will also include a summary and evaluation of the SPPAC, discussion of short- and long-term goals, and relapse prevention strategies (eg, remaining part of the private SPPAC Facebook group). All sessions will be guided by a SPPAC implementation checklist, which the peer trainer will complete during each session. Figure 3 presents an illustration depicting how the components of the SPPAC intervention map onto constructs of self-determination and social cognitive theories to influence motivation and behavior change.

**Figure 3 figure3:**
[figure not shown]
Illustration of how the components of the SPPAC intervention map onto constructs of self-determination and social cognitive theories to influence motivation and behavior change. Figure adapted from Fortier et al [18].

#### Control Group

As suggested for comparisons between experimental and control groups in pilot studies, a pragmatic research approach will be applied to determine if SPPAC is better than usual care for increasing PA [43,44]. Usual care is defined as freely available PA resources that can be accessed by everyone with no special permissions. Therefore, for minimally structuring and standardizing the control group intervention, participants will receive only a handout with existing PA guidelines and a toolkit with recommendations for PA [35]. They will not be given any instruction in how to use the information, but they will not be restricted from the uptake of PA on their own volition.

### Equipment

All participants (experimental and control group) will receive existing PA guidelines and a toolkit with recommendations for PA [35]. Participants in the experimental group will also receive a mobile phone (with a phone number, data plan, and preloaded Facebook apps). Participants may choose to use their personal mobile phone for the study if desired, but will have to download the video calling and Facebook apps and use their own data plan. On provision of the mobile phone, the tester will give instructions in how to use it. In addition, the participant manual will include step-by-step instructions in how to use the mobile phone.

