## Methods

### Trial Design

A two-site (Montreal and Quebec City, QC, Canada), single-blind, pilot RCT will be done to evaluate the efficacy of the SPPAC intervention for increasing PA in an experimental group versus a control group. Participants will be randomly assigned to the experimental group (SPPAC) or the control group (existing PA resources for manual wheelchair users) using a 1:1 allocation ratio (Figure 1). A statistician who is not part of the study team will perform randomization procedures using an undisclosed block size that is stratified by site (19 per site).

After consent and enrollment, a research assistant (RA; research professional with at least 2 years experience in clinical research) will collect baseline data and enter it into a secure database. A research coordinator will inform the statistician of enrollment via telephone or email and will obtain group assignment within 48 hours. The research coordinator will then forward the participants’ contact information to a peer trainer (experimental) and will forward PA recommendations to both groups. To reduce the risk of bias, participants will be instructed not to discuss the study with the RAs (two per site), who will be blinded to group allocation. Experimental group participants will complete 14 SPPAC sessions over 10 weeks [34]. Participants in both groups will receive usual care (ie, existing PA resources/recommendations) [35].

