### Procedure

Outcome measures will be collected at baseline (T1=prerandomization), postintervention (T2=minimum of 2 days and maximum of 10 days), and at 3-month follow-up (T3=retention) (Figure 1). Experimental bias will be minimized by having two trained RAs at each site (one will administer T1 assessments and one will administer T2 and T3 assessments).

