#### Tertiary Outcomes

Tertiary outcomes will evaluate the implementation of the SPPAC program and ensure the SPPAC is delivered as intended. First, the peer trainer will complete a SPPAC checklist for each session, including questions about the logistics of the intervention (eg, time to complete each session, method of contact used) and a list of SPPAC components (eg, goal setting, rewards, skills training). Second, participants in the experimental group will complete a post-SPPAC questionnaire, which asks about attitude about PA, satisfaction with PA, perceived benefits and drawbacks, impact of SPPAC on PA, and changes in views of PA throughout the SPPAC intervention. Third, participants’ reported satisfaction with SPPAC will be collected with the Health Care Climate Questionnaire (HCCQ) [71]. Participants will be asked six questions about their perceived need support from their peer trainer (eg, “My peer trainer listened to how I would like to do things regarding my PA” and “I felt my peer trainer provided me with choices and options about PA”) on a 7-point Likert scale ranging from 1=strongly disagree to 7=strongly agree. High Cronbach alpha levels have been demonstrated [72,73].

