Gathering data on the important theoretical variables that are embedded within the SPPAC program will allow for exploration into mediating influences of complex psychological variables that will further our understanding about best strategies for changing PA behaviors in manual wheelchair users. The authors acknowledge the potential burden of the number of self-reported outcomes and the need for two meetings to collect objective PA data. However, it is anticipated that the self-reported outcomes can be completed in approximately 1 hour, and the tester will travel to obtain the Actigraph from the participants (or provide them with a postage-paid envelope for return to the research center) to reduce burden on participants. Future intervention studies can then integrate the most important behavior change determinants to best individualize PA programs for manual wheelchair users.

In addition to psychosocial factors, intervention dose and content represent important variables that need to be considered when promoting PA uptake and maintenance [78]. The Get in Motion program recommended up to 14 sessions of PA counseling over a 6-month period [11]. However, when asked about preferences for the SPPAC program, participants of focus groups (ie, manual wheelchair users, clinicians, and staff of community-based organizations) preferred that the SPPAC program consist of more contacts within a shorter timeframe [34]. The SPPAC program was designed accordingly [34]. In terms of optimal timing for promoting PA, a recent study among individuals with spinal cord injury suggested that the first 2 months are the most critical for successfully promoting PA [78]. However, a recent peer-led manual wheelchair training intervention showed increased participation in meaningful activities among manual wheelchair users up to 25 years after obtaining a manual wheelchair [31].

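### The Equipment section has the tester, by usage the blinded research assistant, teach participants to use a phone that only the experimental arm receives

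*Protocol article*

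**What the plan says.** **Blinding.** Trial Design in the protocol article describes the study in these terms: "single-blind, pilot RCT will be done to evaluate the efficacy of the SPPAC intervention". It then says who is blinded: "participants will be instructed not to discuss the study with the RAs (two per site), who will be blinded to group allocation". This covers both RAs at a site, with no exception for the one who does baseline.

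**Division of assessments.** Under Procedure, each site's two RAs split the work: "one will administer T1 assessments and one will administer T2 and T3 assessments". T1 is baseline, before randomisation. T2 is postintervention and T3 is the 3-month follow-up. The stated purpose of the split is to limit bias.

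**The phone.** The Equipment section says: "Participants in the experimental group will also receive a mobile phone (with a phone number, data plan, and preloaded Facebook apps"). No phone is provided to controls. The section continues: "Participants may choose to use their personal mobile phone for the study if desired". On instruction it says: "On provision of the mobile phone, the tester will give instructions in how to use it".

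**The tester elsewhere.** The Discussion says that "the tester will travel to obtain the Actigraph from the participants". It also has peer trainers remind participants at every session not to talk about the study with people outside the intervention, and it names testers among them.

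**The concern.** RA blinding is the only blinding the article describes, so the single-blind label depends on it. Teaching someone to use a device issued to one arm only reveals that person's arm. The Equipment section therefore assigns a task that discloses allocation to a role that Trial Design says is blind. This is not a detail left to a fuller document, because the article states both halves of the conflict.

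What is at stake is mainly the secondary outcomes that pass through an interviewer. The Discussion wants effect sizes for primary and secondary outcomes to justify a later trial, and the Secondary Outcomes analysis uses effects on the secondary measures to suggest mediation. Differential interviewing would feed into both.

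**Working it through.** No formula applies and the plan gives no figure to reproduce. The check sets the sections side by side.

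1. **Is the phone tied to allocation?** Yes. Equipment reserves it for the experimental group. Baseline precedes randomisation (Procedure), and the coordinator obtains the assignment after enrolment and baseline (Trial Design). A phone meant for one arm can be handed over only once the arm is known, so the person who explains it learns the arm.

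2. **Is the tester the RA?** The term is not defined, so this is an inference from three uses:
   - Under Primary Outcome Measure, the RA issues the activity monitors. In the Discussion, the tester collects them.
   - In Trial Design, participants are told not to discuss the study with the RAs. In the Discussion, they are told the same about testers.
   - The coordinator, peer trainer, statistician and investigators each have their own label. No separate, unblinded tester is described.

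   The inference is strong.

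3. **Which RA?** Equipment does not say. There are two cases:
   - *The T1 RA.* Baseline is already complete for that participant, so the T2/T3 assessor can stay blind. Trial Design is still wrong about the T1 RA.
   - *The T2/T3 RA.* Both post-randomisation assessments are then done by someone who knows the arm.

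   The text neither assigns the task to the first nor excludes the second.

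4. **How many participants?** 38 participants at 1:1 gives 38 / 2 = 19 in the experimental arm. This is approximate, because 19 per site cannot be halved exactly. It is also a ceiling, because those who use their own phone may not trigger the step. No control triggers it, so the exposure is one-sided.

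5. **Which outcomes are open to bias in the second case?**
   - *Primary outcome.* Activity is recorded by accelerometer, so the assessor has little direct influence.
   - *Mostly self-rated secondary outcomes.* Leisure-time activity, motivation, barrier self-efficacy, wheelchair confidence and need satisfaction are reported by participants, who know which arm they are in.
   - *Interview-type secondary outcomes.* The Wheelchair Outcome Measure (WhOM) is a semistructured interview. The Wheelchair Skills Test-Questionnaire (WST-Q) is described as a structured assessment, although of perceived skills. An interviewer's expectations could influence these two, WhOM more clearly.

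**The case against.** The strongest reply is that the plan already separates baseline from later assessment to limit bias. If the T1 RA hands over the phone, the assessor of every post-randomisation outcome remains blind. The primary outcome is recorded by a device, and most secondary outcomes come from participants who are unblinded whoever explains the phone. Even in WhOM, the participant gives the importance and satisfaction scores. All of this stands, and it limits the consequence. It does not remove the conflict: Trial Design declares both RAs blind, and nothing gives the task to the T1 RA.

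It can also be said that equating tester with RA is an inference. It is, but every other use of the word supports it.

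A reader might infer more than the article supports, in four ways:

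- *That the single-blind property is lost at T2 and T3.* This holds only if the T2/T3 RA gives the instruction, which the text leaves open.
- *That the experimental-only questionnaires are a second route to unblinding.* Tertiary Outcomes says that "participants in the experimental group will complete a post-SPPAC questionnaire" and that the Health Care Climate Questionnaire will also be collected. It names no visit and no administrator for either, so it does not show that an RA handles them.
- *That the RA positions the monitors and could affect the primary outcome that way.* The article says the RA provides them. It does not say who fits them.
- *That the bias can be sized against the mediation rule.* That rule refers to a moderate effect and gives no number, so no such comparison can be drawn from the article.

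**Conclusion.** The point holds as a contradiction between Trial Design and Equipment. Followed literally, the plan reveals allocation to at least one RA declared blind, for each experimental participant who takes a study phone, at most about 19 of 38. This rests on reading tester as RA.

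The effect on results is conditional. If the unblinded RA is the T2/T3 assessor, WhOM and possibly WST-Q are open to assessor bias at both time points. If it is the T1 RA, the post-randomisation assessments can remain blind and only the blinding statement is wrong. Direct bias in the accelerometer outcome is limited in either case. The amount of bias cannot be derived from the article.

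The conflict is worth removing before the first phone is issued, since unblinding cannot be undone. The Results section places the start of enrolment in early 2018, after publication of the article.

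**What to change.** In Equipment, replace the tester with the research coordinator or the peer trainer. Under Trial Design, the coordinator obtains the assignment and passes experimental participants' contact details to the peer trainer, so both already know the arm. Add one sentence stating that whoever provides the phone and explains its use does no T2 or T3 outcome assessment.

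The cost is a small amount of existing staff time and a one- or two-sentence edit. The participant manual already includes instructions for the phone, which keeps the added work low. Outcomes, visits and sample size do not change.

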### Safety

Participating in PA carries innate risks. However, the SPPAC intervention is designed to minimize risks specifically for manual wheelchair users, such as choosing appropriate activities for diagnosis, and selecting appropriate intensity and duration to minimize risk of injury. The SPPAC program incorporates strategies for safe participation, recognizing potentially unsafe situations, and seeking assistance when applicable. Participants will be asked to contact the research coordinator immediately if they experience unusual discomfort or pain. A Data and Safety Monitoring Board (statistician, researcher, health care professional, and manual wheelchair user external to the research team) will meet two times per year during the study to advise regarding safety issues [45].

### Data Collection

All outcome measures are available in English and French. Descriptive characteristics, including age, sex, marital status, education, diagnoses (ie, disability and other diseases that could contraindicate PA participation), and previous manual wheelchair experience (ie, years using a manual wheelchair, where manual wheelchair is used, hours used per day, previous wheelchair skills training received) will be collected in person at baseline by a trained RA. Potentially confounding variables, such as psychological well-being (eg, depression, anxiety) and social support, will also be collected at baseline. Depression is inversely associated with PA participation [46,47] and influences PA for manual wheelchair users [48]. The Hospital Anxiety and Depression Score (HADS), a 14-item (two 7-item subscales) self-report scale, will be used to assess depression and anxiety [49,50]. Social support is also associated with PA participation and well-being [51,52] and will be assessed using the validated 6-item Interpersonal Support Evaluation List (ISEL) [53,54].

#### Primary Outcome Measure

The primary outcome measure, PA, will be measured objectively using actigraphy with a small and lightweight accelerometry-based activity monitor (ActiGraph 3GTX) worn on the body or manual wheelchair that does not impede participation in PA [55,56]. Three-dimensional data are stored in the monitor as “activity counts” [57]. Time between sampling units (epochs) will be set at 15 seconds, allowing the greatest sensitivity for low-intensity activity [58]. In previous studies of manual wheelchair users, concurrent validity was established [58] and instrument reliability of six monitors was high (*r*^2^=.96, *P*<.001) [2].

After completion of all outcome measures at each time point, the RA will provide participants with two actigraphs (one will be positioned on the rear wheel of the manual wheelchair in a waterproof enclosure, the other will be worn on the nondominant arm). Participants will be asked to wear the Actigraph at all times over a 7-day period, except during sleep, bathing/showering, or swimming. Only data from the days in which participants wear the activity monitors for at least 13 hours per day will be included in the analyses [59].

#### Secondary Outcome Measures

Secondary outcomes reflect the proposed theoretical impacts of the SPPAC intervention. Given the dearth of evidence for manual wheelchair users in the literature, there is substantial value in understanding the relationship between PA behavior and the following variables to understand the mechanism of behavior change and to discerning a clinically important impact of the SPPAC program.

The 7-day Leisure-Time PA Questionnaire (LTPAQ) will assess self-reported PA [60]. Participants are asked to recall the frequency (number of bouts) and duration (minutes per bout) of light, moderate, and heavy intensity PA over the past 7 days. Acceptable test-retest reliability and construct validity are documented among manual wheelchair users with spinal cord injury [36,60]. Amount of PA is treated as an ordinal variable (ie, none, low, moderate, high).

The Wheelchair Skills Test-Questionnaire (WST-Q, version 4.2) will be used to assess perceived wheelchair skills capacity and performance [61]. The WST-Q is a structured assessment of 32 discrete mobility skills. WST-Q capacity is scored using a 3-point scale (0=fail; 1=pass with difficulty; 2=pass), with a maximum score of 64. A capacity score is calculated (0%-100%) reflecting the number of skills safely passed. WST-Q performance assesses how often each skill is performed on a 3-point scale (0=never; 1=sometimes; 2=always) and a performance score is calculated (0%-100%). Psychometric properties are documented for manual wheelchair users [62,63].

The Behavioral Regulation in Exercise Questionnaire 2 (BREQ-2) Revised will be used to evaluate PA motivation [64]. Four subscales measure varying degrees of exercise (or PA) regulation: external (eg, “I take part in PA because my family says I should”), introjected (eg, “I feel guilty when I do not participate in PA”), identified (eg, “It’s important to me to be physically active”), and intrinsic (eg, “I take part in PA because it is fun”) regulations. An additional subscale assesses amotivation (eg, “I think PA is a waste of time”). Each subscale contains four items except introjected regulation, which contains three items. Following the statement, “Why do you take part in PA?” participants are asked to respond to each item on a five-point Likert-type scale, ranging from 0=not at all true for me to 4=very true for me. Measurement properties of the BREQ-2 are documented [65].

The Leisure-Time PA Barrier Self-Efficacy Scale (LTPA BSE) will be used to assess self-efficacy to overcome salient barriers to PA participation (eg, when faced with transportation problems) [63]. Each of the six items is preceded with the following statement: “Assuming you were very motivated, how confident are you that you will participate in moderate to heavy leisure-time PA for at least 30 minutes on 3 days per week over the next 4 weeks even if...” Participants will be asked to rate their self-efficacy to overcome each barrier on a scale ranging from 0 to 100 (0=not confident; 50=moderately confident; and 100=completely confident). A mean score is calculated across the six items. The leisure-time PA barrier scale is reliable and valid [60,66].

The Wheelchair Use Confidence Scale-Short Form (WheelCon-SF) will be used to evaluate manual wheelchair use self-efficacy [67]. This 21-item self-report questionnaire reflects one’s current confidence using a manual wheelchair to perform various activities in varying contexts and environments. Each item is rated on a scale from 0=not confident to 10=completely confident, and a score from 0%-100% is calculated. The WheelCon-SF was derived from the original 65-item version, which has documented psychometric properties [68].

The Psychological Need Satisfaction in Exercise (PNSE) Scale will be used to assess the satisfaction of the psychological needs for PA [69]. Participants score 18 items that reflect how he/she might feel when they are physically active on a six-point Likert scale ranging from 1 (false) to 6 (true). A mean score is calculated for autonomy (6 items; “I feel free to exercise in my own way”), competence (6 items; “I feel that I am able to complete exercises that are personally challenging”), and relatedness (6 items; “I feel close to my exercise companions who appreciate how difficult exercise can be”).

The Wheelchair Outcome Measure (WhOM) will be used to assess satisfaction with participation [70]. The WhOM, a client-specific semistructured interview, allows participants to select participation goals that reflect desired outcomes of the intervention. Participants rate the “importance” of the goal (0-10) and their current “satisfaction” with performance of this activity (0-10). Goals are then integrated into the intervention. The WhOM scoring is calculated by multiplying the “importance” by “satisfaction.” Measurement properties of the WhOM have been documented [70].

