Finally, telephone counseling represents an accessible and affordable approach to PA counseling with promising results for increasing PA among manual wheelchair users [10,11]. Opportunely, mobile phones are becoming ubiquitous and afford greater accessibility and convenience for manual wheelchair users. The use of mobile phones for PA counseling may further target autonomy, motivations, and self-efficacy. For example, the use of mobile phones to deliver a PA intervention offers various methods of contact (eg, voice calls, video calls), which may promote personal choice and autonomy. Video calls would enable face-to-face interactions with a peer, which may further enhance self-efficacy and relatedness through vicarious experience. Additionally, social support created by using existing social apps (eg, Facebook) for communicating with peers and monitoring PA goals may provide an avenue for enhancing motivation and self-efficacy [32,33]. For example, results from a recent RCT showed online social networks comprised of like individuals had larger effects on PA than receiving promotional PA messages from a website, and at a much lower cost [33]. Although the source of motivation that arises through online social networks was unclear, the authors suggested that even minimal exposure to online social cues could have a profound influence on PA [33].

The Smartphone Peer Physical Activity Counseling (SPPAC) program will use the power of peers and technology to foster critical psychosocial constructs as a precursor to PA (ie, autonomy, motivation, self-efficacy) providing a potential solution for delivery of broad-reaching and accessible PA intervention for manual wheelchair users with minimal costs. The proposed study protocol will evaluate the efficacy of the SPPAC program for improving PA in manual wheelchair users through a pilot RCT. Based on changes in PA in the intervention group compared to the control group, the primary objective is to provide effect size estimates of the SPPAC intervention on objective PA from baseline to postintervention (10 weeks) and at follow-up (3 months postintervention). Secondary objectives include exploratory evaluation of changes and relationships in subjective PA, wheelchair skills, motivation, self-efficacy (for overcoming barriers to PA, for manual wheelchair use), satisfaction of psychological needs for PA, and satisfaction with participation in PA. Finally, implementation of the SPPAC program will be examined.

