### Sample Size

Based on variability data (mean, standard deviation) from Nooijen et al [39], 30 participants will be required to detect a 28-minute difference per day in PA between the experimental group and the control group (beta=.20, alpha=.05). A sample size calculation for ANCOVA in RCT designs was performed using G*power [40]. Because Arbour-Nicitopoulos et al [11] reported a 26% dropout rate in a telephone-delivered PA intervention for people living with spinal cord injury, the sample size was increased accordingly (total N=38).

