### Statistical Analyses

All data analyses are conducted with SPSS version 23. Multiple imputations are used to treat missing data [74]. Data are screened for statistical outliers and assumptions for each statistical test are examined [75].

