#### Primary Outcomes

Actigraphy data will be imported into Microsoft Excel in the form of activity counts, then cleaned and entered into SPSS for analysis. A mixed-model ANCOVA will be conducted, controlling for the covariates. Summary statistics (mean, SD), effect size (Cohen *d*), and significance testing (*P*) with 95% confidence intervals will be estimated.

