#### Secondary Outcomes

Mixed-model ANCOVA will also be used for significance testing and effect size calculations for all secondary outcome measures. Exploratory analyses will be conducted to investigate the strength and direction of the relationships between the primary and secondary outcomes, looking for moderate-to-strong relationships [76]. If the intervention has a moderate effect on the secondary outcomes and if the secondary outcomes have moderate-to-strong relationships with primary outcome (PA), a potential mediation (exploratory) is suggested.

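### The LTPAQ is declared a four-level ordinal variable but falls under the mixed-model ANCOVA rule for all secondary outcomes, so its effect size would rest on arbitrary category codes although minutes are collected

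*Protocol article*

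**What the plan says.** In the Protocol article, Secondary Outcome Measures describes what the LTPAQ records over seven days: "Participants are asked to recall the frequency (number of bouts) and duration (minutes per bout) of light, moderate, and heavy intensity PA". Weekly minutes can therefore be derived for each participant. The same paragraph then sets the scale for analysis: "Amount of PA is treated as an ordinal variable (ie, none, low, moderate, high". No cut-points between the levels are given.

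Under Statistical Analyses, the Secondary Outcomes paragraph sets the model: "Mixed-model ANCOVA will also be used for significance testing and effect size calculations for all secondary outcome measures". The effect size metric is named in the Primary Outcomes paragraph just before it: "Summary statistics (mean, SD), effect size (Cohen *d*), and significance testing (*P*) with 95% confidence intervals will be estimated". Secondary Outcomes then uses the size of the effect as one condition for suggesting mediation: "If the intervention has a moderate effect on the secondary outcomes", together with a sufficiently strong relationship with the primary outcome.

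The general paragraph adds a check: "Data are screened for statistical outliers and assumptions for each statistical test are examined". It names no alternative model. The Introduction gives the status of the outcome: "Secondary objectives include exploratory evaluation of changes and relationships in subjective PA".

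**The concern.** ANCOVA compares means, so it treats the step from none to low as equal to the step from moderate to high. Declaring a variable ordinal says that the spacing is not meaningful. The article makes both statements about the same outcome. This is a conflict between two stated rules, not a detail left for a later document.

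The trial is a pilot whose declared product is effect size estimates, and the Discussion wants them for secondary as well as primary outcomes. For self-reported PA, the estimate would be a difference in codes such as 0 to 3. It would not be in activity units, and it would change if the boundaries were drawn elsewhere. A later trial could not readily plan from it, and the mediation rule could turn on the coding.

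The conflict is specific to the LTPAQ. The WST-Q, the barriers self-efficacy scale, the WheelCon-SF and the PNSE are scored as percentages or multi-item means, for which ANCOVA is conventional. Only the LTPAQ is expressly called ordinal.

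**Working it through.** **1. The passages side by side.** Data collected: bouts and minutes at three intensities. Analysis scale: four ordered levels. Model: mixed-model ANCOVA for all secondary outcomes. Effect size: Cohen d is named for the primary outcome. Its use here is inferred, because the secondary paragraph says ANCOVA will *also* be used for effect size calculations. Fallback: none named.

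**2. The plan's own figure.** No sample size or power is stated for the LTPAQ. The only figure concerns the primary outcome: "30 participants will be required to detect a 28-minute difference per day in PA". It cannot be reproduced, because the SD comes from a cited study and is not printed. Working backwards with a two-sided ANCOVA F test, 30 participants and 80% power imply d of about 1.06, that is, a residual SD of 28 / 1.06 ≈ 26.4 min/day. Below, this serves only to set 30 / 2 = 15 per arm and one reference effect.

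**3. Information lost by coding.** Assume a normal underlying amount of activity cut into four levels with shares p_k and scores s_k = 0, 1, 2, 3. With cuts c_k, normal density φ and dp_k = φ(c_{k−1}) − φ(c_k), the efficiency of the mean code relative to the uncut value is

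(Σ s_k dp_k)² / Σ p_k (s_k − m)², where m = Σ p_k s_k.

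For equal quarters the cuts are −0.674, 0 and 0.674, with φ(0.674) = 0.3178 and φ(0) = 0.3989. So dp = (−0.3178, −0.0812, 0.0812, 0.3178) and Σ s_k dp_k = −0.0812 + 0.1623 + 0.9533 = 1.0345. The variance of the codes is 1.25. Efficiency = 1.0345² / 1.25 = 0.86.

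| Assumed shares (none/low/moderate/high) | Efficiency | Information lost |
|---|---|---|
| 25/25/25/25 | 0.86 | 14% |
| 40/30/20/10 | 0.83 | 17% |
| 60/20/15/5 | 0.72 | 28% |
| 70/15/10/5 | 0.62 | 38% |

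**4. Power and type I error.** These are simulated two-sample t-tests on a normal underlying value, 10,000 runs per setting, for the first three splits above. With 15 per arm and d = 1.06, power is about 0.80 on the continuous value and 0.71 to 0.75 on the codes. At d = 0.5 it is about 0.26 against 0.22 to 0.23. With no effect, the test on codes rejected in 4.5% to 5.4% of runs with 14 to 19 per arm.

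**5. Dependence on cut-points.** Assume 20% zeros, log-normal minutes otherwise (control log-mean 4, log-SD 1) and a shift of 0.8 log units. Coding the same minutes with upper boundaries at 15/60, 30/90 or 60/180 minutes gives standardised differences of 0.26, 0.36 and 0.43 (in ascending order). With control log-mean 4.5 they run from 0.18 to 0.39.

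**6. Which scale for minutes.** The setting is the same (15 per arm, 20% zeros, shift 0.8), with medians of 30 to 90 minutes and log-SD of 0.8 to 1.2:

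- log(minutes + 1): power about 0.12 to 0.17
- the three codings: about 0.08 to 0.27
- square root of minutes: about 0.20 to 0.32

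In every setting at least one coding matched or beat log(minutes + 1), because that transformation pushes the zeros far from the other values and inflates the variance. The square root beat every coding within each setting. These are t-tests at one time point, not the full mixed model.

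**The case against.** The strongest reply is that little is at stake. The outcome is secondary and exploratory, the primary analysis is untouched, and the mediation step only suggests a possibility. Assumptions will be examined, and a statistical analysis plan that is not shown may fix the scoring or a fallback. A difference in ordered codes still shows direction and rough size. Replacing the codes with minutes is not automatically better, and a proportional-odds model at this sample size may meet sparse cells.

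Much of this stands. It limits the severity and shapes the fix. It does not remove the conflict: checking assumptions does not say what happens to a variable already declared ordinal, and the model sentence admits no exception.

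A reader might go further in four ways that the documents do not support.

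- **Most participants would fall in the two lowest levels.** Entrants must not be meeting PA guidelines, but neither the guideline threshold nor the LTPAQ boundaries are given. The questionnaire also counts light activity, and entry status does not describe later visits.
- **A definite loss of power.** This depends on the zero rate, median, spread and cut-points, none of which is stated.
- **A raised false-positive rate.** The simulation showed none.
- **A weakened relationship with objective PA.** No correlation coefficient is named, so a rank-based one remains open.

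**Conclusion.** The point holds as a conflict between two stated rules for one exploratory secondary outcome. Followed literally, they produce an effect size on arbitrary codes that moves with undisclosed cut-points. In the first illustration it moved by 0.43 − 0.26 = 0.17 with the minutes unchanged. The article gives no numerical threshold for a moderate effect, so a shift of that order could decide whether the mediation condition is met.

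The loss of information is about 14% to 38%. It rests on an assumed normal underlying variable and assumed category shares, so it is a plausible range and not an estimate for this trial. The cut-point results rest on assumed log-normal minutes with 20% zeros. The use of Cohen d for the LTPAQ is the natural reading, not an explicit statement. The harm is to precision and interpretation, and the validity of the test is not in question. The change is worth making because it is cheap, but the primary result does not depend on it.

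**What to change.** Reconcile the LTPAQ paragraph with the secondary analysis sentence.

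- **Preferred.** Analyse total LTPAQ minutes per week in the mixed-model ANCOVA with baseline minutes as covariate, on a scale or model suited to zeros and skew. The square root is one such scale. Avoid log(minutes + 1), which can have less power than the codes when zeros are common. Base the effect size used in the mediation rule on this analysis.
- **If the four levels are kept as a summary.** State the cut-points, exempt the levels from the ANCOVA sentence, and use an ordinal (proportional-odds) model suited to repeated measures, reporting an odds ratio with a 95% confidence interval instead of Cohen d. Note the drawback: 30 participants over two arms and four levels average 30 / 8 = 3.75 per cell at each visit, so some cells may be sparse.

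The cost is a sentence or two of analysis text. The bouts and minutes are already collected, so no data collection or sample size changes.
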